**Methods/design:**

This paper describes the protocol for a double-blinded, sham-controlled, randomized, single-center short term clinical trial in patients with non-specific sub-acute and chronic LBP aged 18 to 70 years. The primary outcome will be the effectiveness of SMATH^® ^versus sham therapy (medical device without active principles) determined by evaluating self perceived physical function with Roland Morris Disability Questionnaire (RMDQ) scores after 4 weeks of treatment (end of treatment). Major secondary outcome will be effectiveness of SMATH^® ^determined by evaluating self perceived physical function comparing RMDQ scores between end of treatment and baseline. The trial part of the study will take 7 months while observational follow-up will take 11 months. The sample size will be 72 participants (36 for each arm). The project has been approved by the Ethical Committee of Cremona Hospital, Italy on 29 November 2010.

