
## Trial Rationale

SMATH^® ^is a new medical device that combines basic principles of mechanical massage, thermotherapy, acupressure, infrared therapy, and moxibustion. SMATH^® ^is included in the "conservative treatments" category [13]. This device is capable of releasing modulated and controlled thermomechanic energy on the patient following a programmable and fully reproducible automatic treatment program selected by the operator. Energy (thermomechanic and infrared) is released at the same time under the spine and legs of the patient. We think this system provides a true automatic multidisciplinary treatment for patients with sub-acute and chronic LBP. The SMATH^® ^system should theoretically be capable of combining the single clinical benefits of massage, thermotherapy, infrared, and acupressure, removing the dependency on operator capability, though obviously missing some elements of human touch, and providing maximum automaticity and reproducibility and producing a real clinical added value for patients. The literature involving different reviews show that little clinical evidence exists on the use of these endorsed therapies on their own. In particular, there is little evidence for massage performed by hands or a mechanical device, or and for superficial heat release [12]. No evidence is available for thermotherapy [13], or for moxibustion, infrared therapy, and acupressure. On the other hand, moderate evidence indicates the effectiveness of multidisciplinary treatment compared to other kinds of active treatment in regards to pain intensity at short-term follow-up [12]. The SMATH^® ^system was developed in an attempt to create an effectiveness advantage by combining different basic theoretical principles. The first clinical results, from the safety clinical study involving 46 patients inside the process to obtain the European Conformity (CE) mark for SMATH^®^, showed the following: RMDQ average score of 10.96 (sd = 3.04; p < 0.05) at baseline and 3.21 (sd = 2.99; p < 0.05) after 3 months, and the average quality adjusted life year (QALY) was 0.46 (sd = 0.13; p < 0.05) at baseline and 0.81 (sd = 0.12; p < 0.05) after 3 months. These data have not been published because they were not suitable for publication and represented the results obtained by one clinical study in which the primary outcome was the demonstration of clinical safety. The internal clinical report concerning this study has been delivered to the notified body in charge of the CE mark process. The SMATH^® ^system obtained the CE mark on 20 December 2010. The current RCT was designed to investigate and test the SMATH^® ^system for use in LBP therapy.

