### Primary outcome

The primary outcome of the trial is represented by the clinical effectiveness of the SMATH^® ^system versus sham therapy after 4 weeks of treatment in patients with sub-acute and chronic non-specific LBP, determined by evaluating self perceived physical function with RMDQ scores. The status of physical function in participants treated with SMATH^® ^interventions will be compared with the status achieved in participants in the sham control arm at the end of treatment (T4) [12].

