### Assessment of outcomes

Four steps of participant examination are planned in this RCT (T1, T2, T3, and T4); during which, general clinical data will be collected about the persistence of LBP symptoms, previous treatment, morphological data, patient activity, blood chemistry tests, anamnesis, and eventual clinically important imaging investigations that were recently done. The effectiveness of SMATH^® ^versus sham will be determined by evaluating self-perceived physical function with RMDQ scores at T4. The secondary outcome of SMATH^® ^therapy effectiveness will be determined by evaluating improvements in patients' motion functionality between T2 and T4 using RMDQ scores. The evolution of pain perception during the study will be measured by VAS scores submitted by the participants at T2, T3, and T4. Quality of life for participants will be estimated by the comparing the EQ-5D questionnaires submitted at the beginning and end of treatment (T2 and T4). During the observational follow-up period all participants will be examined at TF1, TF2, TF3, TF4, and TF5 for general patient status: anamnesis, blood pressure, heart rate in beats per minute, and morphological variables (height, weight, Body Mass Index [BMI]). The RMDQ and VAS questionnaires will be given on the participants at TF1, TF2, TF3, TF4, and TF5, and EQ-5D will be given at TF1, TF2, and TF5. All of the data collected during the study and follow-up will be reported to the CRF.

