### Sample size calculation

Due to the difficulty of finding solid references in the literature regarding the probability of success for different arms of RCTs comparing therapy with medical devices versus sham therapy [19], some basic statistical assumptions have been made in regards to the level of inhibition technically introduced into the SMATH^® ^active principles to obtain a sham device. The therapeutic effect induced by the sham device has been estimated to be 10% of the effect induced by the SMATH^® ^system. Consequently, the probability of SMATH^® ^therapy success has been fixed at 50% (P_1_) [2], whereas a probability of 10% (P_2_) has been fixed for success with sham therapy. Thus, the success difference between the two study arms (P_1 _- P_2_) is 40%. This important delta has been fixed to be statistically significant also in the case of unexpected placebo effect of sham. The false-positive risk factor α (type I error rate) has been fixed at 0.05 (5%). The probability of discovering a difference between the two study arms has been fixed at 90% (study's power). Based on the study's power, (1 - β) = 0.9, the false-negative risk factor rate β is 0.1 (10%). The value of the function *f *(α, β) was calculated by Geigy's tables [23]. Thus, the sample size in each arm of the study (n) should be n = 26. Drop-out has been considered to prevent having an insufficient sample at the end of the study due at the high risk of drop-out of participants in sham arm. A drop-out rate of 15% (0.15) has been estimated based on the literature concerning RCT versus sham in PRM [19]. The sample adjusting factor μ was calculated using the formula μ = 1/(1 - R)^2 ^[24-26], where R represents the drop-out rate. Therefore, μ = 1/(1 - 0.15)^2 ^= 1.3841, and the sample size after correcting for drop-out will be:n# = nμ = 36. The sample of each group will be 36 participants for a total study group of 72 subjects.

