### Statistics and quality

The accuracy and completeness of the collected and registered data will be checked daily by clinical investigators to provide a suitable level of quality for the study. The external monitor will be responsible for arranging random periodic tests of quality throughout the study. In particular, controls will involve the quality and completeness of the CRFs, the treatment execution modalities, the drop-out rate, and correct respect of enrollment criteria application. Data analysis will be conducted using IBMSPSS 19 [21,22]. The morphological and clinical status of participants will be analyzed statistically. Motion functionality, level of pain perception, and quality of life will be evaluated through statistical analysis of the questionnaire scores. Short-term results will be evaluated to elaborate VAS and RMDQ scores, and medium and long-term results will be evaluated by EQ-5D scores, which will also be used to calculate the QALY and incremental cost effectiveness ratio (ICER) index [5,22], which is the most used and suitable index for analyzing the cost/effectiveness of PRM therapies [5]. Pain perception measured by VAS in the different phases and its severity analysis will be evaluated by analysis of variance using SPSS 19. Event incidence (SMATH^® ^versus sham) will be estimated using Kaplan-Meier curves, which will be compared using the log-rank test. Multivariable analysis will be performed using the Cox model.

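### The stated 90% power belongs to a two-proportion test of an undefined success (50% vs 10%), not to the RMDQ score comparison at T4 that is declared primary

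*Protocol article*

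**What the plan says.** The primary outcome is described consistently as an RMDQ score comparison. The abstract (Methods/design) gives it as "evaluating self perceived physical function with Roland Morris Disability Questionnaire (RMDQ) scores after 4 weeks of treatment (end of treatment". The Primary outcome section says that physical function in the SMATH arm "will be compared with the status achieved in participants in the sham control arm at the end of treatment (T4". Assessment of outcomes again refers to "evaluating self-perceived physical function with RMDQ scores at T4". Statistics and quality says that function, pain and quality of life "will be evaluated through statistical analysis of the questionnaire scores". None of these places gives a responder threshold or a proportion.

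The Sample size calculation section uses a different quantity. For the active arm, "therapy success has been fixed at 50% (P_1"; for the control arm, "a probability of 10% (P_2_) has been fixed for success with sham therapy". With a type I error of 5%, it then states: "The probability of discovering a difference between the two study arms has been fixed at 90% (study's power". The result is 26 per arm, multiplied by 1.3841 for 15% drop-out to give 36 per arm and 72 in total. The section gives no RMDQ difference and no SD.

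The only RMDQ SDs in the article are in Trial Rationale, from the 46-patient safety study: "RMDQ average score of 10.96 (sd = 3.04; p < 0.05) at baseline", and 3.21 (SD 2.99) after 3 months. The sample size does not use them.

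**The concern.** A power figure belongs to one endpoint and one test. Here the endpoint that was powered (a binary success) and the endpoint declared primary (the RMDQ score at T4) are different, and nothing in the article connects them. The RMDQ score of at least 4 in Eligibility is an entry criterion at T2, not a success criterion. The secondary outcomes include no responder outcome. The event in the planned Kaplan-Meier, log-rank and Cox analyses is also undefined, so it does not supply the link.

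Two things are at stake. A reader, including those running the health technology assessment that the trial is meant to inform, would take 90% as the power for the primary question, although no RMDQ difference is attached to it. And while success stays undefined, a responder cut-off could be chosen after the data are seen and then presented as the endpoint for which the trial was sized.

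**Working it through.** **Inputs.** P1 = 0.50, P2 = 0.10, α = 0.05, power 0.90, drop-out R = 0.15 (Sample size calculation). RMDQ SDs of 3.04 and 2.99 (Trial Rationale). The article does not state whether α is one- or two-sided; two-sided is used here. SDs of 4, 5 and 6 are assumptions of this review.

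**1. The plan's own figure.** Two proportions, pooled variance under the null, no continuity correction, mean proportion 0.30:

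n = [1.960·√(2 × 0.30 × 0.70) + 1.282·√(0.50 × 0.50 + 0.10 × 0.90)]² / 0.40²
= (1.270 + 0.747)² / 0.16 = 4.070 / 0.16 = 25.4, so 26 per arm.

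Drop-out: 26 × 1/(0.85)² = 26 × 1.3841 = 35.99, so 36 per arm.

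Both figures match. With 26 per arm the power of this test is 90.7%. The stated 90% is therefore the power of a test of two proportions.

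**2. The score comparison with the same N.** Evaluable per arm: 36 × 0.85 = 30.6, taken as 30. For a two-sided 5% two-sample t-test with 30 per arm, the standardized difference detectable with 90% power is d = 0.851. In RMDQ points this is d × SD:

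| SD at T4 | Basis | Detectable difference, 90% power |
|---|---|---|
| 3 | close to the safety-study SDs | 2.55 |
| 4 | assumed | 3.4 |
| 5 | assumed | 4.3 |
| 6 | assumed | 5.1 |

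The difference that goes with 90% power doubles across this range. The article fixes neither the difference nor the SD.

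**3. The same check in the other direction.** Suppose success were a cut on a roughly normal RMDQ score with equal SDs in both arms. Success of 50% and 10% then implies a standardized difference of z(0.50) − z(0.10) = 0 + 1.28 = 1.28. A t-test on the score would have 99.5% power with 26 per arm and 99.8% with 30. Under that reading, sizing on the dichotomy is conservative for the score comparison.

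Steps 2 and 3 bracket the stated 90% from both sides. The article contains nothing that chooses between them.

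**The case against.** The strongest reply is that the sample size is generous for the score comparison. Step 3 of the working gives over 99% power under one natural reading of success. The article's other premises point the same way: the safety study fell from 10.96 to 3.21 (7.75 points), and the sham is assumed to give 10% of the active effect, which implies a difference of 0.9 × 7.75 = about 7.0 points. Even at an assumed SD of 6, 30 per arm would have about 99% power for that. This stands as a reason not to call the trial underpowered, which a reader might infer from the larger detectable differences in the table. It does not show that the power is adequate: the 7.75 points are an uncontrolled change at 3 months, and the article never links success to the RMDQ. The SD of about 3 carries the same caveat, since it comes from that study at baseline and 3 months, not from a controlled comparison at 4 weeks.

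A second reply is that the article condenses a fuller protocol, where success may be defined. That is possible, so the undefined success holds only for the text at hand. But the article sets out both the primary outcome and the whole derivation of N, and as stated they concern different endpoints. A definition elsewhere would not turn the power of a two-proportion test into the power of a score comparison.

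A third reply is that a null result would still be interpretable. This stands: the confidence interval for the RMDQ difference would show which effects are excluded, whatever was assumed at planning.

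**Conclusion.** The point holds in a limited form. The 90% power, with n = 26 and then 36 per arm, belongs to a two-proportion test of an undefined success and cannot be attributed to the between-arm RMDQ comparison at T4. The fault is the mismatch of endpoints; the calculation for the binary endpoint is correct.

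The article does not settle the direction of any error in power. With about 30 evaluable per arm, 90% power goes with a difference of 0.85 SD, which is 2.55 points at SD 3 and 3.4 to 5.1 points at assumed SDs of 4 to 6. These figures assume a two-sided 5% t-test on T4 scores and 15% drop-out. A claim that the trial is too small, or that it is amply sized, would need a target RMDQ difference and a T4 SD, and the article gives neither.

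**What to change.** Keep 72 participants and choose one of two repairs.

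(a) Keep the score comparison as primary and restate its power. Suggested wording: *With about 30 evaluable participants per arm (36 less 15%), a two-sided 5% t-test has 90% power for a difference of 0.85 SD in RMDQ score at T4. This is 2.55 points if the SD is 3.0 (an assumption, based on an uncontrolled safety study at baseline and 3 months), and 3.4, 4.3 or 5.1 points if it is 4, 5 or 6.* Drop the unconditional 90% claim, or confine it to a responder outcome that is defined.

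(b) Define success before unblinding as a stated RMDQ threshold or change at T4, and make the comparison of those proportions the primary analysis. The 90% then applies to it, under the assumed 50% and 10%.

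Repair (a) costs one rewritten paragraph and no extra participants; the stated power becomes conditional on the SD and may look less favourable. Repair (b) changes the primary outcome, so under the Protocol changes section it would go to the ethics committee as an amendment.

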### Statistics and quality

The accuracy and completeness of the collected and registered data will be checked daily by clinical investigators to provide a suitable level of quality for the study. The external monitor will be responsible for arranging random periodic tests of quality throughout the study. In particular, controls will involve the quality and completeness of the CRFs, the treatment execution modalities, the drop-out rate, and correct respect of enrollment criteria application. Data analysis will be conducted using IBMSPSS 19 [21,22]. The morphological and clinical status of participants will be analyzed statistically. Motion functionality, level of pain perception, and quality of life will be evaluated through statistical analysis of the questionnaire scores. Short-term results will be evaluated to elaborate VAS and RMDQ scores, and medium and long-term results will be evaluated by EQ-5D scores, which will also be used to calculate the QALY and incremental cost effectiveness ratio (ICER) index [5,22], which is the most used and suitable index for analyzing the cost/effectiveness of PRM therapies [5]. Pain perception measured by VAS in the different phases and its severity analysis will be evaluated by analysis of variance using SPSS 19. Event incidence (SMATH^® ^versus sham) will be estimated using Kaplan-Meier curves, which will be compared using the log-rank test. Multivariable analysis will be performed using the Cox model.

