### Interventions for each group

Participants assigned to the SMATH^® ^therapy group (A arm) will have 14 treatment sessions of 45 minutes over 4 weeks starting at T2. The treatment module is associated with a dedicated educational booklet for each patient that provides general and behavioral indications for preventing LBP. In this clinical study, the educational booklet will be delivered to all enrolled participants to help them correct their lifestyle during and after the intervention period. In this dedicated booklet, different sections explain to the participants spine anatomy, LBP, LBP prevention, advantages of physical activity, suggestions for positions for walking, sleeping, and to keep weight under control, and exercises to prevent LBP.

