### Secondary outcomes

The secondary outcomes of the trial are: 1) Effectiveness of SMATH^® ^determined by evaluating self perceived physical function comparing RMDQ scores between end of treatment and baseline. 2) Pain perception change from baseline (T2) to end-treatment (T4), evaluated by VAS scores. 3) Quality of life at different steps of the study (T2 and T4), evaluated by EQ-5D scores (QALY). 4) Verified general feasibility of the medical device compared to sham therapy in terms of methodology, sample size, and drop-out rate, among other measures, to constitute a real pilot study and act as a possible reference for future generations of RCTs involving the medical device, conforming to the evidence-based medicine (EBM) criteria for LBP therapy [13] according to the CONSORT statement based on new methodological evidence and to the International Placebo Symposium Working Group recommendations [19].

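### Pain (VAS) is assigned to analysis of variance with no T2 covariate stated; a T2-adjusted model would be more powerful at no cost in data

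*Protocol article*

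**What the plan says.** The Statistics and quality section of the protocol article names one method for pain: "Pain perception measured by VAS in the different phases and its severity analysis will be evaluated by analysis of variance using SPSS 19". It does not say which form of analysis of variance is meant and states no covariate.

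The Secondary outcomes section lists as its second item "Pain perception change from baseline (T2) to end-treatment (T4), evaluated by VAS scores". Under Assessment of outcomes, the course of pain during the trial rests on "VAS scores submitted by the participants at T2, T3, and T4". The Interventions section says that participants in the active arm "will have 14 treatment sessions of 45 minutes over 4 weeks starting at T2", and the sham arm follows the same schedule. T2 is therefore a pre-treatment score in both arms, and T3 and T4 are post-baseline scores from the same people.

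**The concern.** Where a baseline and later scores come from the same person, the usual efficient comparison of randomised arms takes the later score as outcome and the baseline as covariate. The named method does not state this, and its common forms use T2 in a weaker way. Analysis of variance of T4 alone ignores T2. Analysis of the change subtracts T2 in full, which over-corrects unless the correlation is high. A repeated-measures analysis makes T2 one of the outcomes and, in its arm-by-time form, spreads the test over two degrees of freedom.

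At stake is the precision of the pain result in a trial of 36 per arm that expects 15% drop-out. A worthwhile pain effect could be missed when data already being collected would show it.

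**Working it through.** **The plan's own figures.** The documents give no SD, correlation, target effect or power for VAS. The only sample size figure is for success rates of 50% and 10%, with α 0.05 and power 90%. It reproduces: n = [1.96·√(2·0.3·0.7) + 1.2816·√(0.5·0.5 + 0.1·0.9)]² / 0.4² = 25.4, so 26 per arm. The protocol's drop-out factor then gives 26/(1 − 0.15)² = 35.99, so 36. With 15% drop-out, 36 × 0.85 = 30.6, or about 30 completers per arm, which is used below.

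**Assumptions, not in the documents.** VAS SD = 1 at each visit; equal within-person correlation ρ of 0.3, 0.5 or 0.7; arm effect 0 at T2, 0.35 SD at T3 and 0.7 SD at T4; two-sided 5% tests; complete data for 30 per arm.

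**Single-contrast analyses.** Each arm difference has variance (2/30)·V and noncentrality 0.7/√((2/30)·V), where V is
- T4 alone: 1
- change T4 − T2: 2(1 − ρ)
- T4 adjusted for T2: 1 − ρ²

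The noncentralities at ρ = 0.3, 0.5, 0.7 are 2.71, 2.71, 2.71 (T4 alone); 2.29, 2.71, 3.50 (change); and 2.84, 3.13, 3.80 (adjusted). The noncentral t distribution gives power of 76% throughout; 62%, 76%, 93%; and 80%, 87%, 96%. The last row slightly overstates power because it ignores chance T2 imbalance.

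**Repeated measures, arm-by-time.** The arm effects 0, 0.35 and 0.7 have mean 0.35 and sum of squared deviations 0.245. The noncentrality is (30/2)·0.245/(1 − ρ) = 5.25, 7.35 and 12.25, on 2 and 116 degrees of freedom. Power is 51%, 67% and 88%.

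**Simulation, 10,000 trials per setting, 30 per arm.**

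| Analysis | Type I error | Power, ρ = 0.3 | ρ = 0.5 | ρ = 0.7 |
|---|---|---|---|---|
| T4 alone | about 5% | 77% | 76% | 76% |
| Change T4 − T2 | about 5% | 62% | 76% | 93% |
| Repeated measures, arm-by-time | about 5% | 51% | 66% | 88% |
| T4 adjusted for T2 | 5.0–5.2% | 79% | 86% | 96% |

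The closed forms and the simulation agree within about a point. With a first-order autoregressive correlation of 0.7 and no sphericity correction, the arm-by-time test has a type I error of 5.8%.

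**Relative variance.** Adjusted against T4 alone: 1 − ρ² = 0.91, 0.75, 0.51. Adjusted against change: (1 − ρ²)/[2(1 − ρ)] = (1 + ρ)/2 = 0.65, 0.75, 0.85. Adjustment has the smaller variance in every case.

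**Visits pooled as independent rows.** Only under this reading does the arm test become invalid. For three visits the rate is 2·[1 − Φ(1.96/√(1 + 2ρ))] = 12.1%, 16.6% and 20.6%.

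**The case against.** The best defence is that analysis of variance is a family of methods. The wording fits a repeated-measures analysis, and an analysis of the T2-to-T4 change matches the secondary outcome as defined. Both are valid. The article condenses a fuller protocol, and the type of model, covariates and handling of missing visits commonly sit in an analysis plan that is not shown. On this view only a preference for efficiency remains.

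Much of this stands. A reader might infer from the sentence that the three scores will be treated as independent, with an arm test running at about 12–21%. The document neither states nor excludes pooling, so that rate describes a hazard of one reading and not a fault of the plan. A reader might also infer harm from unequal drop-out, since the Sample size section speaks of a high drop-out risk in the sham arm. No differential drop-out was modelled here, and the calculation does not show such harm. Nor is pain the leading secondary outcome: the abstract gives the label of major secondary outcome to RMDQ change, and VAS comes second in the list.

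The gain is also uneven. It is only about 3 points over T4 alone at ρ = 0.3, and about 3 points over change at ρ = 0.7. Part of the gap to the repeated-measures analysis arises because an overall arm-by-time test asks a broader question than a single contrast at T4.

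The defence does not remove the point, because the article does more than stay silent: it names a method. At each correlation tried, the forms tested without T2 as covariate had less power than the adjusted comparison.

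**Conclusion.** The point holds as an improvement to the analysis of a secondary outcome, not as an error that invalidates it. The stated method, in its valid forms, keeps the type I error near 5% but gives up power. Relative to T2 adjustment the loss is about 17, 10 and 3 points for change (79 − 62, 86 − 76, 96 − 93). It is about 3, 10 and 20 points for T4 alone, taking its power as 76% at each correlation, and 28, 20 and 8 points for the arm-by-time test.

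These sizes rest on an assumed 0.7 SD effect at T4, half of it at T3, equal correlations of 0.3 to 0.7 and about 30 completers per arm. A different effect or correlation changes the sizes. For the change and T4-only forms the direction is fixed by the variance ratios at any correlation between 0 and 1. The T2-adjusted comparison of T4 stands in for the T4 contrast of the mixed model proposed below; the mixed model itself was not simulated.

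**What to change.** Replace the VAS sentence in Statistics and quality with text such as: *VAS at T3 and T4 will be compared between the randomised arms in a linear mixed model with arm, visit, arm-by-visit and T2 VAS as covariate, allowing for correlation between visits of the same participant and using all available post-baseline visits. The reported estimate is the arm difference at T4 with its 95% confidence interval.*

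This also settles which analysis is meant and rules out pooling visits as independent. A participant with T3 but no T4 still contributes, under the assumption that missing scores depend only on observed data; someone lost before T3 does not.

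The cost is one sentence. No extra visits, data or software are needed, since SPSS 19 can fit the model with its MIXED procedure. The Protocol changes section counts method of analysis among the changes that may need an ethics committee amendment, so the wording should be submitted that way if the change is judged important, and fixed before allocation is revealed to those analysing the data.

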
The cost/effectiveness ratio for the SMATH^® ^system may also be interesting and could play an important role in the Italian NHS strategy for LBP interventions. An HTA procedure has already been launched in Italy for this new therapy. Like all new technologies and interventions, the clinical effectiveness of the SMATH^® ^system has to be proven by clinical studies in a PRM context. Compared to other medical specialties, PRM has not yet received the recognition deserved from clinicians and researchers in the scientific community, especially for medical devices [19]. We think this unfavorable scenario is due to several reasons, one of which is the lack of high-quality clinical trials in the PRM field. Conducting double-blind placebo-controlled trials in the specialty is difficult; the majority of studies in PRM are practically based on clinical observation, uncontrolled observational studies, or clinical trials comparing two different active therapies. Consequently, these studies are not suitable for providing sufficient proof of efficacy for these therapeutic modalities. The only scientifically recognized way to achieve this goal is to design and manage high-quality double-blind placebo-controlled trials. Sham treatment groups in clinical trials are essential for improving the level of evidence-based practice in PRM. This trial was conceived to reduce the lack of evidence and quality for LBP therapy. No major and minor adverse events or adverse effects have been observed during the use SMATH^® ^on patients with LBP. The SMATH^® ^system has the CE mark as it has passed all tests concerning safety for the patient, operators, and environment. For this reason, no adverse events are expected during this clinical study. However, if adverse events occur, they will be reported to the regulatory authority and ethics committee in accordance with applicable regulations. Trial results will be used to inform HTA procedure already involving SMATH^® ^therapy for health care policies regarding the treatment of LBP in Italy.

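### The article ties SMATH versus sham only to Kaplan-Meier, log-rank and Cox methods for an undefined event, which match neither the fixed-visit RMDQ primary outcome nor the two-proportion sample size

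*Protocol article*

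**What the plan says.** **Outcome.** In the section Primary outcome, functional status under SMATH, measured by RMDQ, "will be compared with the status achieved in participants in the sham control arm at the end of treatment (T4"). Assessment of outcomes repeats this: effectiveness versus sham "will be determined by evaluating self-perceived physical function with RMDQ scores at T4". The secondary clinical outcomes are RMDQ, VAS and EQ-5D at scheduled visits. A fourth secondary outcome is feasibility compared with sham, and it includes the drop-out rate.

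**Sample size.** The Sample size calculation section fixes success at 50% with SMATH and 10% with sham, α = 0.05 and power 90%. It gives 26 per arm, raised to 36 for 15% drop-out. It does not define success on the RMDQ.

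**Analysis.** Statistics and quality makes four relevant statements:
- In general terms, "Motion functionality, level of pain perception, and quality of life will be evaluated through statistical analysis of the questionnaire scores".
- For pain, "Pain perception measured by VAS in the different phases and its severity analysis will be evaluated by analysis of variance using SPSS 19". No arm contrast is stated.
- The incidence of events, with SMATH set against the sham device, "will be estimated using Kaplan-Meier curves, which will be compared using the log-rank test". This is the only statement that names both arms.
- On adjusted analysis, the section says only this: "Multivariable analysis will be performed using the Cox model".

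The article nowhere says what the event is, when its clock starts or how follow-up is censored.

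**The concern.** Kaplan-Meier, log-rank and Cox methods describe the time until something happens. The primary outcome is a score read at one planned visit, and the trial was sized on a difference between proportions. The one method expressly linked to the comparison of arms therefore addresses a third quantity, a hazard, for an event that nobody has defined.

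Two things are at stake. First, a reader cannot tell from the named methods which result answers the primary question. An adjusted analysis by Cox regression cannot estimate the difference in RMDQ at T4. Second, with the event undefined, it could be chosen after the data are seen: response, recurrence, drop-out or adverse event. A log-rank p-value for any of these could then be presented as the SMATH-versus-sham result.

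**Working it through.** **1. What the sample size was built for.** Inputs from Sample size calculation: P1 = 0.50, P2 = 0.10, α = 0.05, power 0.90. Sidedness is not stated; two-sided is assumed. With the pooled proportion p = 0.30:

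n = [1.960 × √(2 × 0.30 × 0.70) + 1.282 × √(0.50 × 0.50 + 0.10 × 0.90)]² / 0.40²
= [1.270 + 0.747]² / 0.16 = 4.07 / 0.16 = 25.4, so **26 per arm**, as stated.

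Drop-out: 26 × 1/(1 − 0.15)² = 26 × 1.3841 = 35.99, so **36 per arm**, as stated.

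A one-sided calculation with continuity correction also gives 26. Under either assumption the basis is a comparison of two proportions at a fixed time. The article gives no hazard ratio, event count or accrual input, so the figure does not come from a log-rank calculation.

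For illustration only: if 50% and 10% were event proportions by T4 under proportional hazards, the hazard ratio would be ln(0.5)/ln(0.9) = 6.58. That would need 12 events in total by the Schoenfeld formula or 20 by Freedman. Neither leads to 26 per arm.

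**2. Three quantities side by side.**

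| Section | Quantity |
|---|---|
| Primary outcome; Assessment of outcomes | RMDQ, SMATH versus sham, at T4 |
| Sample size calculation | Difference between success proportions, 50% − 10% |
| Statistics and quality, the method tied to SMATH versus sham | Time to an undefined event |

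**3. What the event could be.**

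| Possible event | What the article offers | Does log-rank or Cox give the T4 RMDQ contrast? |
|---|---|---|
| RMDQ success | After treatment starts at T2, RMDQ is collected in the randomised period only at T3 (2 weeks) and T4 (4 weeks) | No. There are two possible times, heavily tied and interval-censored. Someone who met a threshold at T3 but not at T4 would count as an event, although not a success at T4 |
| Drop-out | Part of the feasibility outcome; could be timed over the 14 sessions | No. A legitimate secondary analysis, but a different question |
| Adverse event | Trial Rationale: "For this reason, no adverse events are expected during this clinical study", though reporting is provided for | No. Possibly a safety analysis |
| Recurrence in follow-up | Visits TF2 to TF5, after T4, when participants may go on to whatever therapy the investigators indicate | No. This concerns a later period |

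Whichever event is meant, the answer in the last column is the same.

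**4. What fixed-time methods would deliver at the planned size.**
- *Responder proportions at T4, 50% versus 10%:* power is 90.7% with 26 per arm and 97.4% with 36. The sizing stands.
- *Mean RMDQ at T4:* detectable difference at 90% power = SD × √(2/n) × (1.960 + 1.282). Trial Rationale reports SDs of 3.04 and 2.99 from the safety study. With SD 3.0 the result is 2.7 points at 26 per arm and 2.3 points at 36. With SDs of 5 to 6, which are an assumption, it is 4.5 to 5.4 points at 26 and 3.8 to 4.6 points at 36.

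**The case against.** A reader might infer that the trial, run as written, would never test its primary question. The article does not support that. Primary outcome and Assessment of outcomes both plan an RMDQ comparison between arms at T4, and Statistics and quality says that the questionnaire scores will be analysed. Only the test is unnamed, and an article may leave that to a fuller protocol or analysis plan. Nor does any sentence assign the survival methods to the primary outcome. All of this stands.

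It is also fair that the event may be something other than RMDQ success. Drop-out belongs to a stated outcome and can be timed by session, so the limit of two possible times applies only to the RMDQ-success reading within the randomised period. An expectation of no adverse events does not prove that none will occur.

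A further tempting argument is that the expected drop-out in the sham arm makes censoring informative and so biases the log-rank test. That depends on the event: if the event is drop-out, the argument falls. Unequal drop-out would also trouble a T4 score analysis. It is not relied on here.

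What remains is more than missing detail. The article is not silent on method: it commits to a between-arm test and an adjusted model, and neither can estimate the T4 RMDQ contrast.

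**Conclusion.** The point holds as an inconsistency between stated outcome, sizing and named methods. Of the analyses named in the article, none matches the RMDQ comparison at T4 or the two-proportion calculation behind 26 (then 36) per arm. The only method explicitly tied to SMATH versus sham, and the only multivariable model, concern an event with no definition, origin or censoring rule. The conclusion does not depend on which event was intended. It rests on the article alone; a fuller analysis plan, if one exists, may already name the T4 test, but the article's sentences would still need to be reconciled with it. No numerical bias in the result is claimed, and the sample size itself is not in question here.

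**What to change.** Reconcile Primary outcome, Assessment of outcomes, Sample size calculation and Statistics and quality as follows.

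1. State that the primary analysis compares RMDQ between arms at T4, as randomised, by one fixed-time method chosen before outcome data are seen by arm:
   - a linear model giving the mean difference with 95% CI; or
   - to match the sizing, a responder proportion defined in advance on the RMDQ, compared by risk difference or logistic regression.
2. If the mean difference is chosen, add the detectable difference for 36 per arm with the assumed SD, because the present calculation concerns proportions.
3. Replace Cox by the corresponding linear or logistic model for adjusted analysis of the primary outcome.
4. Remove the Kaplan-Meier, log-rank and Cox sentences, or keep them only as a secondary analysis of a named event, such as drop-out or adverse events, with its time origin and censoring stated.

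The cost is a few sentences. If the protocol itself carries the same wording, the change goes to the ethics committee as an amendment under the article's own Protocol changes section. No new data and no more patients are needed.
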